## Abstract

**Background:**

Risk of sarcopenia and poor nutritional status are observed in older adults receiving home care. Hence, the aim of the POWER trial is to investigate the effectiveness of a whey protein oral nutritional supplement (ONS) combined with an online resistance training (RT) programme compared to RT alone on physical function, nutritional status and health-related outcomes in community-dwelling older adults receiving supportive home care who are at risk of sarcopenia.

**Methods:**

This home-based, randomised controlled trial will include older adults aged ≥70 years, receiving supportive home care (professional and/or informal), who will be screened for sarcopenia via telephone. Forty-six participants will be randomised into either (i) ONS + RT or (ii) RT only trial arms. Participants in the ONS + RT group will be provided with a whey protein ONS enriched with leucine and vitamin D to consume day daily for 12 weeks. All participants will be provided with an online RT programme twice weekly via Zoom. The primary outcomes are physical function, measured using the Timed Up and Go test and nutritional status, measured using the Mini-Nutritional Assessment-Full Form. Secondary outcomes include body composition, dietary intake, gait speed, muscle strength, cognitive function, depression risk, activities of daily living, quality of life and feasibility of intervention implementation. All outcomes will be measured at baseline (T1), post-intervention (T2) and 12 weeks post-intervention (T3).

**Conclusion:**

This study will provide data on the effectiveness of a whey protein ONS enriched with leucine and vitamin D combined with an online RT programme delivered via Zoom, compared to the RT programme alone, for older adults at risk of sarcopenia and receiving supportive home care. If effective, this combined approach could act as an important strategy to support maintenance of physical function and nutritional status in older adults, for whom home-based interventions are likely a more feasible option.

**Trial registration:**

NCT05688956; registered December 2022.

## Background

Muscle loss is caused by a discrepancy between muscle protein synthesis and muscle protein breakdown
^
1
^, which can be contributed to by ageing, inadequate nutrition and physical inactivity
^
2,
3
^. Sarcopenia is an age-related condition defined by the European Working Group on Sarcopenia for Older People (EWGSOP) as low muscle strength, mass and physical function
^
1
^. This can lead to reduced ability to carry out activities of daily living (ADLs), falls, loss of independence, hospitalisation, disability and death
^
4,
5
^. When physical function significantly deteriorates, supportive formal or informal home care to perform ADLs may be required
^
6,
7
^.

Currently, the reported prevalence of sarcopenia among community-dwelling older adults (≥60 years) ranges from 5–10%
^
8–
10
^. Within residential care homes, reported sarcopenia prevalence is between 17–73%, and from 22–87% within assisted living facilities
^
11
^. Older adults’ response to protein
^
12–
14
^ and resistance training (RT)
^
2,
15
^ is blunted compared to the response of healthy younger populations. With reduced mobility, anabolic resistance is further exacerbated in older adults
^
13,
16
^. The relationship between sarcopenia and undernutrition is complex, with the development of one interlinked with the other
^
2,
5
^. Undernutrition, mainly when there is insufficient energy and/or protein, contributes to muscle protein breakdown
^
3,
5
^. Older community-dwelling adults receiving home care are more frequently undernourished [14.9%, 95% CI: 9.9–20% compared to those not requiring home care 4.7%, 95% CI: 3.6–6.1%]
^
17
^.

To increase muscle strength and mass, nutritional interventions and/or RT are recommended
^
18,
19
^. The functional benefits of taking part in RT include improved mobility, performance in ADLs, resistance to injuries and falls and enhanced overall quality of life in older adults
^
20–
23,^. Mobility limitations can persist in individuals who are at a higher risk of lower protein intake (<0.8 g/kg adjusted bodyweight/day)
^
24
^. Older females, with higher BMI and poor appetite are at higher risk of inadequate protein intakes
^
25
^. Increasing energy
^
26,
27
^ and protein (1–1.5 g/kgBW/day)
^
26–
28
^ intakes to prevent malnutrition and muscle loss is recommended for older adults
^
26–
28
^. To further stimulate muscle protein synthesis, increasing leucine intake by up to 2.8–3 g twice/day is recommended
^
29,
30
^. Older adults residing in the Northern Hemisphere should also take a daily vitamin D supplement (15 µg for healthy older adults and 20 µg for home bound older adults)
^
19,
31–
33
^. Providing ONS fortified with whey protein, leucine and vitamin D has shown promise in improving health-related outcomes
^
34,
35
^ while such ONS combined with RT in older adults with sarcopenia have shown positive effects on muscle strength, body composition and physical function
^
34
^.

Older adults with sarcopenia, undergoing physical rehabilitation, demonstrated improvements in physical function [Timed Up & Go (TUG) and gait speed) and nutritional status (Mini-Nutritional Assessment-Full Form (MNA-FF)] following 8 weeks of ONS enriched with leucine and vitamin D and supervised RT compared to an isocaloric placebo supplementation and supervised RT
^
36
^. These findings demonstrate the added benefits of nutritional supplementation to improve outcomes of an exercise programme in hospitalised older adults. However, whether similar effects are observed in older adults receiving supportive home care is unknown. Older adults with sarcopenia are recommended to perform at least two RT sessions per week
^
18,
37
^. Given that a number of studies indicate older adults are less likely to engage in exercise programmes for varying reasons
^
38,
39
^, supervised exercise programmes delivered via an online platform are worth considering
^
40,
41
^. Online platforms such as Zoom provide a potential and accessible solution for older adults who have mobility and/or transportation limitations
^
41–
43
^. Providing a supervised and consistent programme can improve adherence
^
44
^ plus the group-based aspect can provide a social element
^
41
^. Recent studies indicate overall acceptability of online exercise programmes among healthy older adults
^
41,
44
^.

Hence, the aim of this study is to test the effectiveness of a new whey protein ONS enriched with leucine and vitamin D (Fortimel Advanced, Nutricia) combined with an online RT programme versus the RT programme alone on the physical function and nutritional status of older adults receiving supportive home care who are at risk of sarcopenia. The primary outcomes of the study are 1) physical function as measured by the TUG and 2) nutritional status as measured by the MNA-FF.

Trial registration:
NCT05688956; registered December 2022.

## Methods

### Study design

This randomised, parallel group, 12-week clinical trial will include 46 community-dwelling (residing in either an urban or rural setting in their own home) older adults who receive supportive home care and are at risk of sarcopenia. Participants will be randomly allocated to either the (i) ONS + RT or (ii) RT only trial arm. Screening potential participants will be undertaken via telephone. Baseline (T1) and follow-up (T2 & T3) assessments will be undertaken in the participant’s own home. Post-intervention (T2) testing will be conducted immediately after the final RT session and again 12 weeks later (T3). The study design and participant flow chart are shown in
Figure 1
^
45
^.

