### Interventions

**
*Oral Nutritional Supplements*
**

Participants randomised to ONS + RT will consume two 200 mL bottles of whey-based protein ONS enriched with the amino acid leucine and vitamin D each day
^
49
^. On exercise days, the first ONS will be consumed at the time of day when the least amount of protein is normally consumed and the second ONS will be consumed as soon as possible after the RT session. On non-exercise days, the most appropriate time for consumption to optimise potential muscle protein synthesis will be based on a 24-hour dietary recall, undertaken at the baseline assessment
^
50
^. The nutritional content of the ONS (Fortimel Advanced, Nutricia) per 200 mL includes: energy: 300 kcal; protein: 20.8 g; leucine: 3 g; fat: 10.4 g; carbohydrate: 30 g; dietary fibre: 2.8 g; vitamin D: 10 µg (Appendix B)
^
45
^.

**
*Dietary advice*
**

All participants and home support person, if required, will be provided with written dietary information (“
Making the Most of Every Bite”, a high energy and protein cookbook, available from the Irish Health Service Executive). Additional dietary advice will verbally be provided to describe protein sources, portion sizes, timings and distribution of protein intake.

**
*Online resistance training programme*
**

A 12-week, progressive, group RT programme, developed with a registered physiotherapist and an exercise physiologist, will be delivered to all participants in their own home via Zoom twice per week by a health science researcher with exercise training (Exercise Instructor). Each RT session will last approximately 45–60 minutes, will include a warm-up and cool-down and moderate to high intensity RT exercises rated on the 10 point Borg Rating of Perceived Exertion (RPE) scale
^
51
^. During the baseline assessment, the exercises will be demonstrated, and the appropriate RT load will be determined using the 5- Repetition Maximum method
^
52
^.

The RT programme will include upper and lower body strengthening exercises, which can be modified to each participant’s muscle function, aiming for 2–3 sets of 8–12 repetitions. Exercises include sit-to-stand, shoulder press, bicep curl, calf raise, leg extension and lateral arm raise. Throughout the sessions, the exercise conducted, weight lifted during the exercise, sets and repetitions performed and RPE will be recorded (

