Table 2). Following the T2 post-intervention assessment, participants will not receive the online RT programme. At the T2 assessment, they will be encouraged to continue to exercise but no additional supervised sessions or support will be provided between T2 and T3.

**Table 2. T2:** Progression plan from week 1 to 12 for the resistance training programme (2 sessions/week).

Phase	Week	Intensity	Duration	Repetitions	Sets	Exercise
Phase 1	Week 1–2	Easy-moderate	45 minutes *	8–10	2–3	Sit-to-stand, Shoulder press, Bicep curl, Calf raise
Phase 2	Week 3–5	Easy-hard	45–50 minutes *	10–12	3	Sit-to-stand, Shoulder press, Bicep curl, Calf raise
Phase 3	Week 6–8	Moderate-hard	60 minutes *	12	3	Sit-to-stand, Shoulder press, Bicep curl, Calf raise, Leg extension, Lateral arm raise
Phase 4	Week 9–12	Moderate-hard	60 minutes *	12	3	Sit-to-stand, Shoulder press, Bicep curl, Calf raise, Leg extension, Lateral arm raise

*Rest period is the same throughout the whole programme: 1–2 minutes between sets; 2–3 minutes between exercises and at least 48 hours between sessions

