### Statistical analysis plan

Statistical analyses will be performed using SPSS Statistics for Windows, version 27 (SPSS Inc., Chicago, Ill., USA) and RStudio (2023.06.2. Posit, PBC) as appropriate. Data cleaning will be conducted prior to analysis.

Demographic data and study primary and secondary outcomes will be described using measures such as mean and standard deviation, median and interquartile range, 95% confidence interval, or count and percentage. Descriptive statistics will also be used to report the feasibility of the intervention. Missing data will not be imputed for the primary analysis.

Data will be analysed using the intention-to-treat approach, wherein all participants who have been randomly allocated to the study intervention
^
80
^ will be included. The between-group and within-group difference at baseline (T1), post-intervention (T2) and 12-weeks post-intervention (T3) in primary and secondary outcomes will be analysed using either parametric or non-parametric, based on the normality of data distribution. The primary outcome is TUG and MNA-FF post-intervention (T2). Further, a mixed between-within linear model will be used to assess group, time, and group x time interaction effects. Between-group linear mixed-model analysis will be used to assess the mean difference in change from baseline to post-intervention. The dependent variables will be TUG and MNA-FF with group (ONS + RT, RT), time (baseline, post-intervention), and the group-by-time interaction as fixed factors; participant ID as a random factor; and baseline values as covariates. Effect sizes (partial eta squared) will be calculated using the Cohen’s d classification (0.01 = small, 0.06 = moderate, 0.14 = large). Variables not normally distributed will be transformed as appropriate. The proportion of participants whose TUG and/or MNA-FF improved or deteriorated post-intervention (T2) will be calculated. The interindividual variability in response to the ONS will be calculated using the Atkinson and Batterham formula
^
81
^.

Using the same approach as above, between-group differences and within-group differences at baseline (T1), post-intervention (T2), and 12 weeks post-intervention (T3) will be analysed for secondary outcomes.

A per-protocol analysis will also be conducted, including participants who adhered to the intervention and have baseline (T1) and post-intervention (T2) measurements
^
82
^.

A p-value of less than 0.05 will be considered statistically significant.

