^ and sarcopenia RT prescription recommendations
^
18
^. This intervention will provide a structured, supervised exercise programme, encouraging participants to stay committed, which will aid adherence
^
44
^. Exercises will be appropriately modified and monitored throughout the intervention. As with other programmes delivered via an online platform, a limitation to this study will be that some older adults will not have access to Zoom (via laptop or tablet), therefore limiting their ability to participate. However, it provides a viable alternative for those unable to access a centre or facility for in-person RT programmes
^
91
^.

Assessments 12 weeks post-intervention (T3) will examine the long-term effects once the intervention ceases. Although participants may show good adherence to the online RT programme, they may discontinue RT once the programme stops
^
92
^. Therefore, the sustained effects of the interventions on physical function, nutritional status and health-related outcomes will be examined 12 weeks post-intervention.

A limitation of this study includes lack of a placebo supplement; therefore, intervention blinding will not be possible. A specific stipulation by the UCD Ethics Committee, given the vulnerability of the study population, was that dietary advice should be provided to all participants to promote an increase of dietary protein through food sources. Providing dietary advice to all participants may act as a confounding factor, making it challenging to isolate the effects of the ONS from changes due to the dietary advice. In addition, as both groups are undertaking the online RT programme, following a similar design to previous research in a vulnerable population
^
36
^, the effectiveness of the RT programme alone compared to no exercise is not possible to determine. However, in addition to the primary analysis comparing the outcomes between ONS + RT versus RT alone, the statistical approach will allow for main effects of time to be identified across both groups, which can be interpreted in relation to minimal clinically important differences. Furthermore, collecting biomarkers of muscle protein synthesis or 25-hydroxyvitamin D (25(OH)D) level will not be possible. Older adults who are housebound in Ireland are recommended a daily supplement of 20 µg of vitamin D, due to limited sun exposure and insufficient intake through food
^
33

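### T2 is fixed immediately after the last training session with no rest interval, so acute exercise effects can enter the within-group changes and the T2 to T3 comparison, though not, if equal in both arms, the primary between-group contrast

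*Protocol article*

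**What the plan says.** The protocol article, Study design, sets the timing in one sentence: "Post-intervention (T2) testing will be conducted immediately after the final RT session and again 12 weeks later (T3". The same section places every assessment at home: "Baseline (T1) and follow-up (T2 & T3) assessments will be undertaken in the participant’s own home". The Statistical analysis plan makes this the decisive visit: "The primary outcome is TUG and MNA-FF post-intervention (T2".

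Table 2 describes sessions in weeks 9 to 12 as "Moderate-hard 60 minutes", with three sets of 12 repetitions of six exercises, including sit-to-stand, calf raise and leg extension. Its footnote asks for at least 48 hours between sessions. Under Interventions the programme "will be delivered to all participants in their own home via Zoom twice per week", so both arms train alike. No trial sessions are supplied after T2. The same section has the exercises demonstrated and the load set by 5-repetition maximum at the baseline assessment, without saying whether this precedes or follows the outcome tests.

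For exercise days in the ONS + RT arm, "the second ONS will be consumed as soon as possible after the RT session".

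The Discussion commits to two uses of change over time. It expects "main effects of time to be identified across both groups, which can be interpreted in relation to minimal clinically important differences", and it says that "the sustained effects of the interventions on physical function, nutritional status and health-related outcomes will be examined 12 weeks post-intervention".

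**The concern.** TUG, gait speed and sit-to-stand use the same movements and muscles as the final session. If assessors follow the sentence literally, T2 is measured in a post-exercise state and T3 is not, while the state at T1 is undefined. A change between visits then mixes the effect of 12 weeks of training with the effect of the preceding hour.

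At stake are the analyses that compare a participant or an arm with itself: the T1 to T2 and T2 to T3 changes, the time effect set against minimal clinically important differences, the proportion whose TUG improved or deteriorated at T2, and the question whether gains last to T3.

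The sentence also meets the supplement instruction. In one arm only, a bottle is due at the moment testing, including weight and bioimpedance, is due. The article does not say which comes first.

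**Working it through.** **Step 1: where an acute shift goes.** Let e1, e2 and e3 be the mean acute exercise effect on TUG, in seconds, at T1, T2 and T3. No trial session precedes T3, so e3 = 0 as far as trial exercise is concerned.

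- Observed T1 to T2 change in an arm = true change + (e2 − e1).
- Observed T2 to T3 change in an arm = true change − e2.
- Time effect (T1, T2) averaged over arms = true effect + (e2 − e1).
- Between-arm difference at T2 = true difference + (e2 in ONS + RT − e2 in RT).

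If e2 is the same in both arms, the last bracket is zero. A constant added to every T2 value changes neither a difference in means nor a rank test.

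**Step 2: size for the within-group analyses.** The documents give no value for e2. Assume 0.5, 1 or 2 s of slowing, with e1 = 0.

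| Assumed e2 | Added to T1 to T2 change | Added to T2 to T3 change | Added to between-arm difference |
|---|---|---|---|
| 0.5 s | +0.5 s | −0.5 s | 0 |
| 1 s | +1 s | −1 s | 0 |
| 2 s | +2 s | −2 s | 0 |

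For scale, 5% of the lower reference time under Timed Up and Go is 0.05 × 9.2 = 0.46 s, and 15% of the higher one is 0.15 × 11.3 = 1.70 s. The percentages are assumptions, and those reference times are not this population's TUG times. If T1 testing follows load setting, e1 is not zero and the first column shrinks to e2 − e1.

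**Step 3: noise in the primary TUG contrast.** Sample size gives 15 per group for 3.7 s, 80% power and p<0.05, but no standard deviation (SD) or sidedness, so the figure cannot be reproduced independently. Solving the two-sided two-sample t test backwards gives a standardised difference of 1.06 to 1.10, so an SD of 3.7/1.10 = 3.36 to 3.7/1.06 = 3.49 s. With 3.49 s and the planned 23 per group, power is 94%. (A one-sided reading implies an SD of 3.83 to 3.98 s and power of about 93%.)

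If fatigue or delay varies between people with SD s, the total SD is √(3.49² + s²).

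| Extra SD at T2 | Total SD | Power, 23 per group |
|---|---|---|
| 0 | 3.49 s | 94.0% |
| 0.5 s | 3.53 s | 93.6% |
| 1 s | 3.63 s | 92.2% |
| 2 s | 4.02 s | 86.2% |
| 3 s | 4.60 s | 76.0% |

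**Step 4: if the shift differs by arm.** With no true effect, an arm difference in e2 of 0.5 s gives a rejection rate of about 7.6%, and 1 s gives about 15.8%, instead of 5%. These are what-if figures; nothing in the article shows such a difference.

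**Step 5: is exposure uniform?** Classes are run for a group over Zoom and testing is a visit to each home, so the delay is likely to vary. Adequate attendance is 18 of 24 sessions and the intention-to-treat set keeps everyone randomised, so some participants may miss the last class and be tested rested. This supports the noise in Step 3, but does not by itself create an arm difference.

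**The case against.** The strongest reply is that *immediately* is meant on a scale of weeks. The sentence goes on to a visit 12 weeks later, Table 3 and Data collection say only post-intervention, and same-hour home testing after a group class would be hard to arrange. This stands as a reason for doubt about what will happen. It does not repair the text, which names the session rather than the programme and gives no window.

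The second reply is that the trial compares two arms that do the same training. This stands in full: a reader might infer that the primary comparison is contaminated, but a common shift cancels there. For the same reason it would be wrong to express a slowing of 0.46 to 1.70 s as a share of the 3.7 s target. One is common to both arms; the other is a difference between them.

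Third, MNA-FF, the other primary outcome, consists of questions and anthropometry and is not plausibly moved by fatigue. This also stands.

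Fourth, a reader might take T1 as exertion-free and conclude that improvement is certainly understated and maintenance certainly overstated. The article supports neither step. Load setting takes place at the baseline assessment, sessions contain a cool-down and rest periods, and no passage gives the direction of the acute effect.

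Fifth, the drink. Nothing says that it is taken before weighing. If it were, 200 mL would add roughly 0.2 kg to a secondary outcome in one arm, which is minor.

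**Conclusion.** The point holds in a limited form. The article fixes the primary visit by a rule that, taken literally, tests participants in a different physical state at T2 than at T3, and in an undefined state at T1. The within-group changes, the time effect read against minimal important differences, the improved or deteriorated proportions and the sustained-effect question would absorb the acute effect: e2 − e1 from T1 to T2, which is the whole of e2 if T1 is rested, and −e2 from T2 to T3. Its size and direction are unknown; 0.5 to 2 s for TUG is an assumed range.

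For the primary TUG contrast the consequence is noise. The loss is small unless the extra SD is large: 94% to 92.2% at 1 s, and 76.0% at 3 s, given the back-solved SD of 3.49 s. Bias there needs fatigue or delay that differs by arm, which the documents do not show. The documents do not support calling the trial's main comparison invalid. The change is worth making because it is cheap and protects analyses to which the protocol commits itself.

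**What to change.** - In Study design, replace the present timing with a rested T2 window, for example 48 hours to 7 days after the last session. The lower limit matches the spacing between sessions in the Table 2 footnote.
- State that the functional tests precede the 5-repetition-maximum load setting at T1.
- Use the same pre-test conditions at T1, T2 and T3, and record the interval since the last session at T2.
- Reconcile the T2 timing with the instruction on the second ONS after a session. This concerns when the measurement is taken; the supplement schedule need not be altered for it.

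The cost is a scheduling change in the protocol and one recorded variable. The downside is up to a week's delay before T2. The status of ONS in that interval must be stated, since it concerns one arm only, and it should be said whether the 12 weeks to T3 run from the last session or from the T2 visit. If participants have already been tested under the present sentence, record which timing applied to each, so that the two conditions can be told apart in the analysis.
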